## Abstract

**Background:**

Acute respiratory infections (ARIs) are frequent reasons for medical consultations in general practice and can lead to unnecessary recontacts. Introducing new point-of-care (POC) polymerase chain reaction (PCR) diagnostic equipment may offer an attractive and efficient way of providing a more precise and exact microbial diagnosis. Successful uptake of POC PCR equipment could potentially lead to a reduction in recontacts with benefits for both staff and patients. However, introducing new diagnostic technology is a complex intervention and several contextual factors may impact the implementation.

**Objective:**

This study aims to evaluate the effect of POC PCR test availability in general practice on the subsequent (1) number of recontacts to the general practitioner (GP) for patients with symptoms of ARIs (primary outcome) and (2) hospital admissions, deaths, antibiotic prescriptions, health-related quality of life, GP and patient satisfaction, costs, cost-effectiveness, and contextual facilitators and barriers conditioning the implementation process (secondary outcomes).

**Methods:**

This study is a cluster-randomized, crossover, nonblinded superiority trial with a 1:1 allocation ratio between usual care (control) and POC PCR test availability (intervention). Questionnaire data are collected at day 0, 7, 14, and 28 after the initial contact (health-related quality of life, absenteeism and presentism among patients, and patient satisfaction) and after finalization of the study period (GP satisfaction). Data on recontacts, hospital admissions, redeemed antibiotic prescriptions, costs, and deaths will be retrieved from the Danish national registries. The implementation process will be evaluated based on data from interviews with users of POC PCR tests (i.e., GPs, staff, and patients) and from observations in the clinics in line with Medical Research Council guidelines.

**Results:**

As per the randomized crossover design carried out during September 2023 to March 2024 investigating a sample of 100 GP clinics, we expect to obtain an in-depth and multifaceted understanding of the effects of the availability of the POC PCR test equipment in general practice.

**Conclusions:**

This study will provide valuable information about the diagnostic conditions and possibilities in general practice and provide insights into the organization of primary health care.

**Trial Registration:**

ClinicalTrials.gov NCT06120153; https://clinicaltrials.gov/study/NCT06120153

**International Registered Report Identifier (IRRID):**

DERR1-10.2196/72842

## Introduction

### Acute Respiratory Infections, Recontacts, and Antibiotic Prescriptions

A very common reason for visiting Danish general practice is symptoms of acute respiratory infections (ARIs), and diagnostic accuracy is important to ensure appropriate treatment [1]. Danish general practitioners (GPs) handle approximately 98% of these cases without referring the patients to further diagnosis or treatment in hospitals [2]. It is important for the quality of care that patients are diagnosed as fast as possible, and that the GP and the patient are confident about the diagnostic accuracy. If not, the patient may be unnecessarily worried and contact health services again. Recontacting health services is sometimes appropriate, for example, if the patient’s symptoms worsen. Unnecessary recontacts are, however, unsatisfactory to both the patient and the clinician as a high number of recontacts indicate diagnostic and treatment deficits and a lack of reassurance of the patient. In addition, recontacts and hospital admissions are costly for society. For these reasons, the study investigates the following research question: “Do patients with ARIs diagnosed in general practice with access to point-of-care (POC) polymerase chain reaction (PCR) equipment benefit in terms of reducing recontacts to general practice in a 1-week period after the initial contact?”

In addition to investigating recontacts as the primary outcome, the study also allows for insights into patterns related to antibiotic prescription. In Denmark, around 75% of all antibiotics are prescribed in general practice, and ARIs are some of the most common reasons for prescriptions [3,4]. Even though Denmark is among the countries with the lowest consumption of antibiotics worldwide, there is still room for improvement in the total use of antibiotics and in the choice of regime, that is, broad spectrum versus narrow spectrum antibiotics [5]. Antibiotic overuse may lead to microbial resistance, and if the overall consumption is not restrained, infections with resistant bacteria will be a major problem for both the individual patient and the health care system. Hence, initiatives to significantly reduce the prescription and use of antibiotics are highly warranted [6]. Whether symptoms arise from bacteria or from a viral infection is often uncertain in the primary care setting [7], and when precise diagnostics are desirable, it often takes 1 to 3 working days and requires sending test samples to external laboratories. Due to diagnostic uncertainty, GPs may in some situations prescribe antibiotics even in cases where the patient’s symptoms are caused by a viral infection. Introducing POC PCR diagnostic equipment in general practice may improve diagnostic accuracy, and thereby reduce revisits as well as prescription and use of antibiotics.

Introducing practice changing diagnostic tools into primary care extends beyond the mere adoption of a new diagnostic technology; it is a complex intervention that involves significant interactions among health care professionals, technology, and the health care system itself. Complex interventions are characterized by multiple components that interact within their implementation context [8]. These include the behaviors of health care providers and patients, the environment in which the intervention is deployed, and the outcomes it aims to influence. The complexity of integrating, for example, POC PCR testing into daily practice is particularly evident in the multifaceted processes it entails, from conducting the test and interpreting its results to making informed clinical decisions and adapting the health care infrastructure to support its use.

The use of rapid PCR testing for respiratory tract infections has been extensively examined in hospital and emergency department settings [9]. The effects on clinical and resource related outcomes vary significantly between studies [10-12]. A recent systematic review and meta-analysis found no association between rapid PCR testing and antibiotics use, return visits, length of stay, or hospitalization among patients with ARI in emergency departments [13]. The clinical effects of POC PCR testing of patients with ARI in general practice have not been extensively examined. However, a feasibility study conducted during the COVID-19 pandemic showed promising results in terms of feasibility and clinical utility [14,15].

This paper describes a protocol for a cluster randomized controlled trial focusing on the effects of introducing POC PCR testing (Cobas LIAT) for ARIs in general practice in Denmark. To qualify the study protocol, 2 preparatory studies were conducted, demonstrating barriers and facilitators for introducing POC PCR technology in general practice, including user experiences from the clinicians [16,17].

### Objectives

The study is organized in 3 work packages (WPs) with the following objectives.

#### WP1: Effectiveness of POC PCR Availability for ARI in GP Clinics

The following are objectives 1 to 6: to evaluate the effectiveness of POC PCR availability in general practice on (1) the number of recontacts to the GP for patients with symptoms of ARIs (primary outcome); (2) the number of redeemed antibiotic prescriptions, (3) health-related quality of life, and (4) GP and patient satisfaction. In addition, (5) the number of hospital admissions and (6) deaths are included as safety measures.

#### WP2: Cost-Effectiveness Associated With POC PCR Availability in GP Clinics

The following are objectives 7 and 8: to evaluate (7) the costs and (8) the cost-effectiveness of POC PCR availability in general practice compared with usual care.

#### WP3: Process Evaluation of Introducing and Implementing POC PCR Availability in GP Clinics

The following is objective 9: to identify and analyze contextual facilitators and barriers as well as behavioral factors that influence potential uptake of the implementation process tied to the POC PCR equipment.

This study uses recontacts as a primary outcome of evaluating the effectiveness of the test, as this is a less-explored phenomenon associated with ARIs. Denmark is already one of the countries with the lowest consumption of antibiotics, which is why this measurement is also included in the study (as a secondary outcome in the analyses). While investigating patterns tied to antibiotic prescriptions are important, the scope of this study is to explore the wider operations of a general practice setting, which a primary but not isolated focus on recontacts allows.

## Methods

### Study Setting

The study is conducted in 4 Danish regions (Region of Southern Denmark, Region Zealand, North Denmark Region, and Central Region of Denmark), comprising a general population of approximately 4 million individuals and 2340 GPs [18].

In Denmark, GPs receive reimbursement from the administrative regions for all consultations and tests included in the collective agreement between the PLO and the regions. The role of the regions in this study is to create and administer project specific reimbursement codes that will enable calculations of the number of patients with ARIs and the number of POC PCR tests performed. All Danish GPs are accustomed to register reimbursement codes in their electronic patient record system after each consultation, and all codes are linked to the patient’s personal identification number.

### Recruitment and Eligibility Criteria

GP clinics are eligible for participation if they are situated in one of the participating regions and receive reimbursements from the administrative regions. GP clinics are invited by letters with written information about the project. The letters are sent from the clinical trial unit at the University of Southern Denmark (SDU), who also conducts follow-up phone calls and distributes additional material if requested by the clinic. Interested GP clinics will sign a collaboration agreement with SDU and receive additional information. Patients are eligible for participation if they contact a participating GP clinic with symptoms of ARI during the study period. All clinics and patients taking part in the effect study and the economic evaluation (WP1 and WP2) will receive information about the project and data collection according to the Danish Data Protection Act Section 10. Specifically, as the studies of WP1 and WP2 are conducted on register data, no patients will be identifiable, and thus, no consent is needed. The qualitative process evaluation (WP3) necessitates oral and written information, and all patients are asked to sign an informed consent form. All participation is voluntary, and every patient and professional is informed that they can revoke their consent at any point should they regret their participation.

### Allocation

The study is designed as a cluster randomized crossover study with the GP clinic as the unit of randomization, that is, all GPs affiliated to a GP clinic are randomized to either intervention (A) in the first period and usual care (B) in the second (AB sequence) or in the BA sequence. Allocation of the general practice clinic is randomized using a computer algorithm and allocation is 1:1 between the AB or BA sequence. When an eligible clinic commits to the trial, the project statistician informs the project management about the next allocation in the allocation sequence and the clinic is randomized according to this, that is, blinded randomization allocation is used.

Randomization at the patient level is not considered feasible, as an ongoing randomization procedure in the clinic would be time consuming and pose a risk of bias and interference with the diagnostic procedure and subsequent decision-making by the GP.

Therefore, randomization is stratified by type of clinic, that is, partnership- or single-physician clinics. Large collaborative clinics are randomized as one unit in the group of non–single-physician clinics. A block randomization in blocks of 10 is used.

### Intervention

#### Pretrial Information and Training

The study will be conducted over a period of 25 weeks (Figure 1).

**Figure 1 figure1:**
[figure not shown]
Illustrates the phases in the randomized controlled trial’s control and intervention periods as well as the washout period. In the washout period, Roche removes, cleans, and reinstalls the equipment from the intervention group, so it is ready for the control group for the final phase of the trial.

In the month leading up to the intervention period, the POC PCR device will be installed in the intervention clinics by staff from Roche Diagnostics A/S, and assays and equipment necessary for the testing will be sent to the clinics free of charge. Just before entering the trial period, each clinic will be trained by staff from the clinical trial unit from SDU. During the training session, the clinic will receive further information about patient inclusion, registration of eligible patients in the reimbursement system, and whether the clinic is about to enter an intervention period, including training on how to perform the POC PCR tests. In addition, all clinics will receive an information poster for patients to display in the waiting area. All GP clinics will receive a fee of DKK 6000 (approximately €800 or US $840; 1DKK= US $0.14) for participating in the study. In addition, GPs will be remunerated for performing the test (DKK 71.48 [approximately €9.50 or US $10] per test equivalent to already established POC tests). The clinics participating in the process evaluation will receive another DKK 1000 per interview (approximately €134), and DKK 2000 (approximately €268 or US $280) per whole day during observation studies.

An overview of the pretrial activities is presented in Textbox 1.

Pretrial instructions and training during intervention and control periods.
**Intervention period**
Introductory instructions about the trial are provided for the clinics (how to include and register patients with acute respiratory infection [ARI])Training in the use of Cobas LIAT respiratory testing portfolio (group A Strep, Influenza A/B, SARS-CoV-2, and respiratory syncytial virus)Instruction to include all patients contacting the clinic with symptoms of ARI during a 7-wk period and possible point-of-care testing, if deemed relevant
**Control period**
Introductory instructions about the trial are provided to the clinics (how to include and register patients with ARI)Instruction to include all patients contacting the clinic with symptoms of ARIs during a 7-wk period for treatment as usual.

#### Activities During the Study Period

All patients with ARI contacting the participating GP clinics during the intervention or control period will be included in the study. Before or after the consultation with the GP, the clinic staff will hand out information materials about the project, including a leaflet with a QR code and a link to a questionnaire.

In the control period, patients with ARI will receive usual care, usually comprising no or limited diagnostic tests at the clinic, or nasal or pharyngeal swap for testing at an external laboratory with an expected response time of 1 to 3 days. During the intervention period, the POC PCR equipment will be used when the GP deems it relevant.

Developed by Roche Diagnostics A/S, the POC PCR test system tested in this study comprises an analysis instrument and assay tubes for testing (1) StrepA, (2) Sars-Cov-2 and Influenza, and (3) Influenza or respiratory syncytial virus (RSV). The test is performed on oropharyngeal (StrepA), nasopharyngeal (SARS-Cov-2 or Influenza, and Influenza or RSV), or nasal (Influenza or RSV) swap samples. Running the test takes approximately 20 minutes per assay.

After the consultation, the GP registers the project specific reimbursement codes in the electronic patients record system. Three different reimbursement codes are used: the first code is for the registration of each individual patient with ARI contacting the clinic. This code is used in both control and intervention periods. The second code is for each time the POC PCR test is performed (allowed only once per patient per consultation even though it is possible to perform multiple tests within the same consultation), and the third code is for situations where the test result is conveyed by phone or email to the patient the day after the test is performed. The last two codes are for intervention periods only. GPs are only remunerated for performing the test.

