#### Blinding (Masking)

Due to the intervention procedure (an oropharyngeal, nasopharyngeal, or nasal swab) and the use of project specific reimbursement codes, it is not possible to blind the patients and GPs.

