#### Register Data

Comprehensive public register data on contacts and services provided in primary care, prescription of antibiotics, and hospital contacts and various characteristics of the GP clinics will be retrieved from the Danish Health Data Authority [20]. Furthermore, information on morbidity, socioeconomic status, and various demographic characteristics on each patient will be obtained from Statistics Denmark [21]. Data from the different registers are linked by the patients’ personal identification number. No data will be retrieved from the registers until the protocol paper is accepted for publication.

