### Data Analysis

#### Effectiveness of GP Access to POC PCR

Demographic characteristics of the included patients and GP clinics will be presented. Analysis of the binary primary outcome uses a standard logistic regression model on the individual (contact) level, accounting for clustering of patients in clinics by generalized estimating equations. Primary analysis will follow an intention-to-treat approach, and we want to show superiority. A corresponding analysis strategy will be applied for hospital admissions, deaths, and redeemed antibiotic prescriptions. A level of 5% will be set as statistically significant. Analyses will be performed with the most recent version of Stata (StataCorp).

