### Strengths and Limitations

First, there is limited possibility to ensure that the patient receives the postcard and fills out the questionnaire, which may hamper studying the patients’ quality of life and satisfaction. Second, the quality of the quantitative data is highly dependent on GPs applying the project specific reimbursements codes to all relevant patients. As coding after each patient contact is everyday routine for Danish GPs, the coding practice itself is not a new task for the participating clinics. However, coding difficulties associated with the new reimbursement codes cannot be ruled out, which may in turn lead to a slight underreporting. Finally, while the POC PCR test equipment allows for conducting 5 ARI tests, the current test portfolio does not allow testing for, for example, pertussis and mycoplasma. As such, it could influence both the professional and patient experience and perception of what is considered quality and precise diagnostics and, by the mere introduction of increased testing that the POC PCR equipment promotes, the introduction of more testing could lead to an overemphasis of testing for the sake of testing. Moreover, it takes 20 minutes to run a test and a consultation in a Danish general practice usually is reimbursed for only 10 minutes. This practical factor may also influence the uptake of the intervention and the experience of the usefulness of the technology, it may even create additional workload in the clinic.

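### Entry to the analysed sample rests on post-consultation coding by unblinded GPs, which may differ between a clinic's two periods, and the primary model described uses none of the register covariates already obtained

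*Protocol article*

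**What the plan says.** The Allocation section describes a "cluster randomized crossover study with the GP clinic as the unit of randomization". A clinic receives its sequence when it commits to the trial, before any of its patients is identified. Under Blinding (Masking) the article states that "it is not possible to blind the patients and GPs".

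Activities During the Study Period sets out how patients enter the data: "After the consultation, the GP registers the project specific reimbursement codes in the electronic patients record system". Of the three codes, "the first code is for the registration of each individual patient with ARI contacting the clinic"; it is used in both periods. The other two codes, for a test performed and for a result conveyed the next day, belong to intervention periods only. On payment: "GPs are only remunerated for performing the test". Pretrial Information and Training gives the amount as DKK 71.48 per test, and adds a flat DKK 6000 for every clinic.

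Textbox 1 instructs clinics in both periods to include all patients with ARI symptoms. Strengths and Limitations concedes that data quality depends heavily on GPs applying the codes and that difficulties with the new codes may arise, "which may in turn lead to a slight underreporting".

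On the model: "Analysis of the binary primary outcome uses a standard logistic regression model", at contact level, with generalized estimating equations for clustering in clinics. Patient and clinic characteristics are to be presented. Register Data says that "information on morbidity, socioeconomic status, and various demographic characteristics on each patient will be obtained from Statistics Denmark". Within-Trial Cost-Effectiveness adjusts the economic models for health care cost in the 6 months before the initial contact and for baseline utility.

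**The concern.** Randomising clinics balances clinics. It does not balance patients who are identified later by staff who know which period they are in. Here the act that identifies a patient, entering the ARI code, comes after the consultation and after any decision to test.

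The two periods also differ in what surrounds that act. In an intervention period a tested patient calls for a second, paid project code, which may prompt the GP to enter the ARI code as well. In a control period nothing comparable prompts it. If that changes who is coded, the periods compare different kinds of patient, and a difference in recontacts can appear, or be hidden, without any effect of the test.

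The Strengths and Limitations section treats incomplete coding as a general loss of data. For a between-arm comparison, the question is whether the loss differs between periods, and that is not considered. The primary model as described makes no use of the patient data that could absorb part of such a difference.

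**Working it through.** **1. The planned effect and precision**

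Inputs from Sample Size Calculation: recontact proportions 0.32 and 0.28 (difference 0.04), significance level 0.05 (taken as two-sided), power 0.80, within-period correlation 0.02, across-period correlation 0.01, 108 clinics with 50 contacts each, 100 clinics chosen. The 50 contacts are read as the total, so m = 25 per clinic-period; at m = 50 per period the formula below gives only 61 clinics.

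Variance of one clinic's period difference, with v0 = 0.32 × 0.68 = 0.2176 and v1 = 0.28 × 0.72 = 0.2016:

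(v0 + v1)/m × [1 + (m − 1) × 0.02] − 2 × 0.01 × √(v0 v1)
= 0.4192/25 × 1.48 − 0.00419 = 0.02063

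Clinics = (1.960 + 0.842)² × 0.02063 / 0.04² = 101.2. With the control variance in both arms it is 105.0, and with a t correction as well (clinics − 2 degrees of freedom) it is 108, the stated figure. The sample size is not in dispute. At 100 clinics the standard error is √(0.02063/100) = 0.0144 and the power about 79.5%.

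**2. What differential coding would do (assumed values)**

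The article gives no figure for coding completeness by period, so these are illustrations. Suppose the test has no effect, control periods show 0.32, and intervention periods code an extra fraction *a* of patients whose recontact risk is *q*. Then

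shift = (0.32 + a q)/(1 + a) − 0.32 = a (q − 0.32)/(1 + a)

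| a | q | Shift | Share of 0.04 |
|---|---|---|---|
| 0.10 | 0.20 | 0.10 × (−0.12)/1.10 = −0.0109 | 27% |
| 0.20 | 0.15 | 0.20 × (−0.17)/1.20 = −0.0283 | 71% |
| 0.10 | 0.44 | 0.10 × (+0.12)/1.10 = +0.0109 | 27%, opposite sign |
| 0.20 | 0.49 | 0.20 × (+0.17)/1.20 = +0.0283 | 71%, opposite sign |

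The last two rows mirror the first two around 0.32.

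**3. Consequence for the test**

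With 100 clinics and 25 contacts per control period, recomputing the variance for the altered sample, and with no true effect:

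- Row 1: standard error 0.0143. The chance of a significant result favouring the test is Φ(0.0109/0.0143 − 1.96) = 12%, against a nominal 2.5%.
- Row 2: standard error 0.0140, chance 53%.

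In the other direction, suppose the true reduction is 0.04 and coding shifts the intervention rate upwards. Keeping the standard error at 0.0144, power falls from 79.5% to Φ((0.04 − 0.0109)/0.0144 − 1.96) = 53% for a shift of 0.0109, and to Φ((0.04 − 0.0283)/0.0144 − 1.96) = 13% for a shift of 0.0283.

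**4. What the described model can absorb**

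The primary model names a correction for clustering only. Demographic, morbidity and socioeconomic variables are to be obtained for each patient, and prior 6-month cost is used in the economic models. These variables predate the contact, so coding behaviour cannot alter them. Symptom severity at the contact is not among the register data listed, so selection on severity would be absorbed only in so far as it follows the recorded variables.

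**The case against.** **Safeguards.** Clinics are trained and told to include every ARI patient in both periods, the same ARI code serves both, and each clinic is its own control. This counts for something: the crossover removes stable differences between clinics in coding habit. It does not remove a change within a clinic from one period to the other. An instruction carried out by unblinded staff does not exclude such a change, and the article itself expects incomplete coding. Intention-to-treat does not help, because uncoded patients never enter the sample.

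**Payment.** A reader might infer that ARI coding is paid in intervention periods and unpaid in control periods. The article does not say so: the ARI code is unpaid in both, the DKK 6000 fee is the same for all clinics, and the test fee is described as matching established point-of-care tests. The article also notes that a 20-minute run time against a 10-minute reimbursed consultation may hold back uptake. What stands is narrower: the only per-item payment tied to project coding occurs in one arm.

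**Direction.** A reader might infer that the extra patients would be milder and the bias would favour the test. Nothing in the document supports that. GPs test when they deem it relevant, so a test may equally prompt coding of sicker or more uncertain cases.

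**Silence on covariates.** The article never calls the model unadjusted, and an unseen analysis plan may add covariates. It would be wrong to conclude that adjustment has been ruled out. However, the article positively describes the primary model and, in the next section, specifies baseline adjustment for the economic models. The problem of how patients enter the sample stands whatever the analysis plan says.

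**Conclusion.** The point holds as a risk that the plan under-describes and could cheaply reduce. The documents establish the mechanism: unblinded GPs, a sample-defining code entered after the consultation, a paid test code in one arm only, and a limitations section that does not consider differences between periods. They do not show that differential coding occurred, or which way it would act.

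The size is unknown. Under the assumed values the shift is 1.1 to 2.8 points in either direction, or 27% to 71% of the 4-point effect. Those shares depend entirely on the assumed extra fraction and risk.

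Covariate adjustment is worth making but is not a cure, since severity at contact is not among the listed register data. The comparison of coded numbers and case mix is therefore needed alongside it. The change should be made, but the point does not invalidate the design.

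**What to change.** Before register data are retrieved, which the Register Data section places after acceptance of the protocol paper:

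1. Adjust the primary logistic GEE for a short, prespecified set of pre-contact variables (age, sex, morbidity, socioeconomic status, health care cost in the prior 6 months) and for the clinic-type stratum used in randomisation.
2. Report a standardised risk difference with the adjusted odds ratio. The adjusted odds ratio is conditional on the covariates, whereas the trial was sized on 0.32 against 0.28.
3. Keep the model without covariates as a sensitivity analysis.
4. Tabulate the number of ARI-coded patients and their baseline profile by clinic-period and arm, so that a change in coding is visible.
5. State in Strengths and Limitations that underreporting may differ between periods, and that adjustment cannot fully correct for selection on severity at contact.

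The cost is a little analysis work and a few sentences. The variables are already due to be obtained, and clinics need do nothing more.
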